### Exclusion criteria

Exclusion criteria are limited to patients: (1) aged < 18 years or > 80 years; (2) diseases receiving preceding systemic therapy with glucocorticoids, such as chronic kidney disease, inflammatory disease, or other immune system related diseases; (3) anesthesiologist judge that the subjects cannot use the dexamethasone, such as diagnosed with epilepsy or active ulcer; (4) intraoperative findings of extra-hepatic disease before intervention, need to undergo a synchronous resection for other organs except gallbladder; (5) intraoperative findings of additional lesions before intervention, need to combine with other procedures, such as ablation or bilo-enteric anastomosis; (6) unable to provide informed consent.

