### Randomization and blinding

Once informed consent is provided, patients will be assigned randomly in a 1:1 ratio to the dexamethasone group or the control group on the day when they accept surgery. The computer-generated numbers are prepared by a research statistician and kept inside sealed envelopes by a research assistant who is not physically present in the operating room. Block size will not be disclosed to preserve allocation concealment.

When the patient enters the operating room, a research assistant will open the corresponding opaque envelope containing the patient allocation status and assigned medication. Then, the research assistant will refer the assigned medication to the anesthesiologist and remind them to inject the medication 10 min before IPM. The medication container, appearance, dosage, and technique of administration will be the same for two groups. Patients, surgeons, nursing team, anesthesiologists, and outcome assessors will be blinded to the study allocation status. If there is a situation such as a medical need or emergency which required unblinding, the principal investigator will be informed and make the final decision and report to the ethics committee.

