### Intervention

Perioperative care and intraoperative technique for both study groups follow the routine practice of the surgical team. Patients in the dexamethasone group will receive intravenous administration of 10 mg dexamethasone (dexamethasone sodium phosphate injection, 1 ml:5 mg) 10 min before IPM. Patients in the control group will receive intravenous administration of 2 ml saline 10 min before IPM. All the patients will get routine postoperative rehabilitation management, and their relevant concomitant cares are homologous.

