### Statistical analysis

The trial is designed to test the superiority of dexamethasone to placebo with respect to the primary outcomes and secondary outcomes with the use of difference analysis. Superiority with respect to the primary outcomes are required before the secondary outcomes could be tested. All included participants will provide 80% power to detect superiority with respect to the primary outcomes. The AUC of ALT and AST will be tested for superiority, analyzed by Student’s *T* test or the Mann-Whitney *U* test.

Continuous variables will be presented as the mean ± standard deviation or median with its range based on normality testing and compared by an independent sample Student’s *T* test or the Mann-Whitney *U* test. Categorical variables will be presented as number (percentage) and compared using chi-square test or Fisher exact test. The modified intention-to-treat (ITT) principled analysis is applied for allocating patients into the group; moreover, when compliance is at a low level or the trial is no longer double-blinded, the as-treated (AT) analysis will be added to be supplements. Sensitivity analysis of missing data (loss to follow-up, death, withdrawal, etc.) will be conducted with the multiple-imputation approach. All tests for differences except primary outcomes are two-tailed and considered statistically significant if *P* values < 0.05. Bonferroni correction will be performed to correct for four primary outcomes statistically. We have changed the adjustment for multiple testing after 16 July 2023. All statistical analyses are performed by the SPSS version 20 and GraphPad Prism version 8.0.1.

As appropriate, the significance of postoperative categorical complications will be analyzed using chi-square test or Fisher exact test or will be tabulated and summarized using descriptive statistics.

Besides, according to the extent of resection and background of hepatic fibrosis after surgery, subgroup analysis will be performed to assess the protective effect of administration of dexamethasone before clamping the hilar pedicle on residual liver injury after undergoing liver resection with 25-min hepatic inflow occlusion.

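### The as-treated supplement for low compliance is not protected by randomisation and can be biased in either direction; a complier-average estimate would answer the same question

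*Protocol article*

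**What the plan says.** All references are to the protocol article.

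- **Analysis set (Statistical analysis).** "The modified intention-to-treat (ITT) principled analysis is applied for allocating patients into the group". The next clause provides that "when compliance is at a low level or the trial is no longer double-blinded, the as-treated (AT) analysis will be added", as a supplement. The article does not spell out what the modification is, what counts as low compliance, or how as-treated groups are formed. A condensed article may leave such detail to the full protocol or the analysis plan.
- **Timing of allocation (Randomization and blinding).** Patients are "assigned randomly in a 1:1 ratio to the dexamethasone group or the control group on the day when they accept surgery". "When the patient enters the operating room, a research assistant will open the corresponding opaque envelope", and the assistant hands the drug to the anesthesiologist with a reminder to "remind them to inject the medication 10 min before IPM". Surgeons, anesthesiologists and outcome assessors are blinded.
- **Control treatment (Intervention).** "Patients in the control group will receive intravenous administration of 2 ml saline 10 min before IPM". A dose can therefore be missed in either arm.
- **Eligibility settled in the operating room.** Inclusion criterion (1) requires a clamping interval of at least 25 minutes. Among the exclusions are "intraoperative findings of extra-hepatic disease before intervention" and additional lesions that call for further procedures.
- **Non-adherence that the article describes (Follow-up management and withdraw criteria).** The examples are refusing the seven-day blood sampling and receiving targeted therapy or immunotherapy after surgery. Data from withdrawn patients are recorded but not analysed.

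**The concern.** An as-treated analysis differs from an ITT analysis only if some patients did not receive what they were allocated. In this trial the dose depends on an event during the operation, the start of clamping, and the allocation is already open by then. A patient can be randomised and never reach the injection for reasons connected with how the surgery went. The same surgical course plausibly drives ALT and AST, which supply all four primary outcomes.

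In the usual sense of the term, a dexamethasone patient who was never injected counts as untreated and joins the controls, who already include any undosed saline patients. The dexamethasone group then contains dosed patients only, while the control group mixes dosed and undosed patients. The two groups can differ in surgical course as well as in drug. For a given prognostic gap, the distortion grows with the undosed share, so it is largest when poor dosing compliance is the reason for running the analysis. At stake is a supplementary result that could be cited for or against the ITT-based result without reflecting the drug's effect.

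**Working it through.** **1. The plan's own figure.** The Sample size section gives an SD of 184.684 for peak ALT, a target difference of 58.882 IU/L, 1.645 and 0.84 as the normal deviates, and about 10% dropout.

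n per group = 2 × (184.684 × (1.645 + 0.84) / 58.882)² = 121.5, so 122. Dividing by 0.9 gives 136; multiplying by 1.1 gives 135. The stated 135 per group is reproduced, so the SD and the target difference can serve as the scale below.

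**2. Set-up.** Let δ = 58.882 be the true reduction in dosed patients. Let q be the undosed share, taken as equal in both arms because those giving the dose are blinded. Let D be the mean peak ALT of undosed minus dosed patients apart from any drug effect. Neither q nor D is in the documents; both are assumptions. Write μ for the mean of dosed saline patients.

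**3. Estimates (control minus dexamethasone), with N randomised per arm.**

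- As-treated: the control group has N(1 + q) patients, of whom 2qN are undosed, so its mean is μ + 2qD/(1 + q). The dexamethasone group has mean μ − δ. The difference is δ + 2qD/(1 + q).
- ITT: (μ + qD) − (μ + qD − (1 − q)δ) = (1 − q)δ. D cancels.
- Complier-average: ITT divided by the dosed share, (1 − q)δ / (1 − q) = δ.
- Injected patients in both arms: μ − (μ − δ) = δ.

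**4. Size of the as-treated shift, 2qD/(1 + q).** D is set to 0.5 SD (92.342) and 1 SD (184.684), with both signs. Percentages are of 58.882.

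| q | 2q/(1+q) | D = ±92.342 | D = ±184.684 |
|---|---|---|---|
| 2% | 0.0392 | ±3.6 (6%) | ±7.2 (12%) |
| 5% | 0.0952 | ±8.8 (15%) | ±17.6 (30%) |
| 10% | 0.1818 | ±16.8 (29%) | ±33.6 (57%) |
| 20% | 0.3333 | ±30.8 (52%) | ±61.6 (105%) |

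With D = 0 the shift is zero at every q.

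**5. One case in full, q = 10%.** The ITT difference is 0.9 × 58.882 = 53.0, and the complier-average and injected-only differences are 58.9. The as-treated difference is 58.9 − 33.6 = 25.3 if undosed patients are 1 SD lower, and 58.9 + 33.6 = 92.5 if they are 1 SD higher. A simulation of the lower case (135 per arm, 4,000 trials) gave mean differences of 25.4 (as-treated), 53.4 (ITT) and 59.1 (injected only). In the higher case with no drug effect, the false-positive rate at an unadjusted one-sided 5% level is about 0.42 (normal approximation, 135 per arm).

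**The case against.** The case against is substantial.

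- **Eligibility removes many of these patients.** Someone who is not clamped for 25 minutes, or whose operation changes because of findings before the dose, fails the criteria. The article does not say whether the modified ITT set drops them. This stands: the point reaches only those who remain in the analysis set.
- **The regrouping is not in the text.** The article never says that undosed dexamethasone patients are counted as controls. Because control is a real saline injection, as-treated could mean grouping by injection received, with undosed patients in neither group; in the set-up above that is unbiased. This also stands, so the point is conditional on the usual meaning of the term.
- **The non-adherence described is postoperative.** Refusing blood samples or starting other therapy after surgery changes nobody's injection, and loss of blinding alone creates no undosed patients. In those situations an as-treated analysis moves no one and causes no bias of this kind.
- **The consequence is small.** The analysis is a conditional supplement. The complier-average estimate is essentially the ITT result rescaled, and adds little new evidence on superiority.

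A reader might go further and infer that an undosed patient must be one who escaped ischemia, so that the as-treated analysis would necessarily hide a true benefit. The documents do not support this. They give no reason for a missed dose. An omission or supply error would put D near zero, and clamping too early to leave the 10-minute window would leave an undosed patient with full ischemia. Neither the sign nor the size of the bias can be fixed from the article.

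**Conclusion.** The concern holds as a minor, conditional point. If some patients in the analysis set miss the injection, and as-treated is applied in its usual sense, the supplementary comparison loses the protection of randomisation. It can then be biased either way by 2qD/(1 + q). With 10% undosed and a gap of 0.5 to 1 SD, that is about 17 to 34 IU/L on peak ALT, or 29% to 57% of the 58.882 target; with no prognostic gap it is nil. These sizes rest on assumed values of q and D and on equal omission in the two arms. The 10% in the Sample size section is dropout, not missed dosing, and lends q no support. The primary modified ITT result is not altered.

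**What to change.** For the low-compliance trigger, replace the as-treated supplement with a complier-average causal effect. Use randomised arm as the instrument for dexamethasone received, fit by two-stage least squares, and report it beside the modified ITT result. Blinded saline makes it credible that allocation acts only through the drug. A simpler alternative is to compare patients who received the blinded injection in both arms, which relies on omission being unrelated to arm.

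Possible wording:

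> If patients in the analysis set did not receive the assigned injection, the effect of dexamethasone in those who would receive it will be estimated with randomised arm as instrument for receipt, and reported beside the modified ITT estimate. This replaces the as-treated analysis for low compliance and was decided after unblinding on 16 July 2023.

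The date matters: the article already records changes after 16 July 2023 to the primary outcomes and to the multiplicity adjustment, and this would be a further one.

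The cost is a sentence, one extra model and a wider interval. Treating q as known, the complier-average interval is 1/(1 − q) times the ITT interval, so 1/0.9 = 1.11 times at 10% undosed and 1/0.8 = 1.25 times at 20%. The estimate is a difference in means, so it will not match a Mann-Whitney result where the plan uses that test.

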### Follow-up management and withdraw criteria

We will develop a rigorous follow-up plan to improve the follow-up rate and ensure data quality. Plans are as follows: (1) for subjects: excluding patients with inconsistent family opinions and unwillingness to be included in the screening process, strengthening subjects’ education in the informed consent process, and promoting communication with subjects of the time and content of review after the surgery and physical state after discharge; (2) for researchers: introducing dedicated personnel for follow-up management and dealing with the follow-up tables; (3) for information management: applying app software for follow-up management, developing a personalized follow-up management system. E-visit, a platform focused on patient clinical trials, supports patient original case upload, patient outcome report, follow-up management and doctor-patient interaction, various message reminders, and so on.

Participants will be allowed or required to withdraw from the RCT if the following are met: (1) they do not follow the treatment plan strictly (such as refusing continuous 7 days of collecting blood sample, receiving the targeted therapy or immunotherapy after surgery) while participating in the RCT, and (2) subjects are required to leave the RCT, such as participants cannot accept continuous 7 days of collecting blood sample or postoperative follow-up. For participants who withdraw from the RCT, we plan to record some routine postoperative testing indicators, including hepatocellular injury parameters (ALT, AST, and their peak value) and liver function indexes (TBil and international normalized ratio (INR)). Besides, postoperative complications, postoperative hospital stay, and 30- and 90-day mortalities are also recorded. However, these data will not be analyzed.

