### Outcome measures

All blood samples will be collected on PODs 1, 2, 3, 4, 5, 6, and 7 following the same procedure for performing serial laboratory evaluation. All blood samples will be collected at 7 a.m. every day, which then will be sent by the outcome assessor to the Department of Experimental Medicine for examining by a fixed physician. Preoperative laboratory parameters are viewed as baseline of postoperative laboratory parameters (if the postoperative stay is not more than 7 days, outcome assessors will be responsible for the subjects for blood sample collection).

Primary outcomes are as follows: peaks value of ALT and AST and AUC of ALT and AST.

Indicators of hepatocellular injury are as follows: ALT and AST of postoperative 7-day both the two groups; then, we will calculate the mean for postoperative 7-day after surgery to depict the line charts with mean ± stand error.

Peak values of ALT and AST as well as AUC values of the postoperative 7-day course of ALT and AST (peak value is defined as the maximum value measured in 7 days, and AUC is calculated by the value of postoperative 7 days). The magnitude of the effect of glucocorticoids on relieving surgical pressure and alleviating ischemia-reperfusion injury are assessed by the AUC surrounded by continuous ALT and AST, which is the metrics for declaring superiority of the tested intervention.

We decided that peaks value of ALT and AST and AUC of ALT and AST were primary outcomes after 16 July 2023.

Secondary outcomes:Intraoperative blood lossLiver function: assessed by measuring serum level of TBil and INR for coagulationInflammatory cytokines: assessed by IL-6, PCT, CRP, and their respective peaksPostoperative complications: according to the Clavien–Dindo grade, including major complications and minor complicationsPostoperative hospital staysMortality: defined as in-hospital death or death within 30 or 90 days after surgery

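### ALT and AST values recorded for withdrawn patients are kept out of the analysis and multiple imputation is only a side check, so the main comparison is in effect of completers

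*Protocol article*

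**What the plan says.** The Outcome measures section takes blood on each of postoperative days 1 to 7 and reduces the series to one peak and one area per enzyme: "peak value is defined as the maximum value measured in 7 days, and AUC is calculated by the value of postoperative 7 days". It also makes the outcome assessors responsible for the samples of patients who stay no more than seven days.

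The Statistical analysis section compares these derived values between arms: "The AUC of ALT and AST will be tested for superiority, analyzed by Student’s *T* test or the Mann-Whitney *U* test". On the analysis set it says "The modified intention-to-treat (ITT) principled analysis is applied for allocating patients into the group". Imputation appears once: "Sensitivity analysis of missing data (loss to follow-up, death, withdrawal, etc.) will be conducted with the multiple-imputation approach".

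The section on follow-up management and withdrawal gives examples of not following the plan that allow or require withdrawal: "refusing continuous 7 days of collecting blood sample, receiving the targeted therapy or immunotherapy after surgery". It continues: "For participants who withdraw from the RCT, we plan to record some routine postoperative testing indicators". The list that follows names ALT, AST and their peak values, as well as bilirubin, INR, complications, hospital stay and mortality. The paragraph ends: "However, these data will not be analyzed".

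**The concern.** A ground for withdrawal is tied directly to the primary outcome: a patient who will not give all seven samples can be taken out of the trial. This happens after randomisation, and willingness to go on giving blood may depend on how recovery is going, hence on treatment and enzyme course. The plan still records ALT and AST for these patients, then bars their use. What remains for the main test is the group that stayed to the end, which is not the group that was randomised.

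The two sections also sit badly together. One sets aside the recorded values of withdrawn patients. The other lists withdrawal among the causes of missing data to be imputed. Taken literally, observed enzyme values are discarded and replaced by imputed ones, and only in a secondary analysis.

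**Working it through.** **Step 1. The passages side by side.**
- Withdrawal section: refusing the draws can lead to withdrawal; ALT, AST and peaks are recorded; they are not analysed.
- Statistical analysis section: modified intention-to-treat; two-sample test on one value per patient; imputation only as a sensitivity analysis, with withdrawal named as a cause.
- Result: a withdrawn patient contributes nothing to the main test, even where enzyme values exist. If the imputation did draw on those values, the statement that they are not analysed would be untrue. On either reading the two sections need reconciling.

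**Step 2. The plan's own sample size.** Inputs from the Sample size section: SD 184.684 and target difference 58.882 IU/L (peak ALT), one-sided 5% (1.645), 80% power (0.84), dropout about 10%.
- n per arm = 2 × (184.684 × (1.645 + 0.84) / 58.882)² = 121.5
- 121.5 / 0.9 = 135.0

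The stated 135 per arm is reproduced. The 10% allowance therefore fits a plan in which such patients leave the analysis. With 121 to 122 analysed per arm, power for peak ALT at the unadjusted one-sided 5% level is 79.8% to 80.1%. The allowance protects power; it does nothing about bias.

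**Step 3. Possible bias in the peak ALT difference.** Let a share p of an arm be missing and let the unseen patients' mean lie k SDs above that of the seen patients. The arm's completer mean is then too low by p × k × SD. The error in the difference (dexamethasone minus control) is

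bias = (p_control × k_control − p_dex × k_dex) × 184.684.

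The values of k, and the split of missingness by arm, are assumptions; the documents give neither.

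| Missing per arm | Shift | k = 0.25 | k = 0.5 | k = 1 |
|---|---|---|---|---|
| 10% and 10% | one arm only | 4.6 | 9.2 | 18.5 |
| 5% and 15% | both arms | 4.6 | 9.2 | 18.5 |
| 10% and 10% | both arms, equal | 0 | 0 | 0 |

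Entries are absolute values in IU/L. In the first row, 0.10 × 0.25 × 184.684 = 4.6 and 0.10 × 1 × 184.684 = 18.5. The second row uses (0.15 − 0.05) and gives the same products. As shares of the target: 4.6 / 58.882 = 8%, 9.2 / 58.882 = 16%, 18.5 / 58.882 = 31%. The sign depends on which arm loses more, or sicker, patients. The documents give no SD or target for AUC, so the same sum cannot be done for it.

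**The case against.** The strongest reply is that this is a condensed article. A complete-case main analysis with imputation as a sensitivity analysis is a legitimate design, and the scoring of partial series, the imputation model and the pooling method usually sit in an analysis plan that is not shown. All of that stands, and none of it is counted here. Sampling after discharge is also arranged, so early discharge need not cause gaps, and about 10% dropout is budgeted. Routine values from withdrawn patients may not make a full seven-day series.

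What the reply does not reach is the stated decision to record these enzyme values and not use them. That is written in the article, not left open by it. Arranged sampling does not cover refusals, and an incomplete series is a reason to impute the missing days, not to discard the days in hand.

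Three stronger readings are tempting and are not supported:
- **That the imputation is offered as a test of missing at random.** The article states no such purpose. Standard imputation rests on that assumption, but as a contrast to completers it is still useful.
- **That incomplete series will be scored too low.** No scoring rule is given, and the direction is not fixed. For an assumed ALT course of 300, 250, 180, 130, 100, 80, 65 IU/L the trapezoid area is 922.5. Omitting day 3 and joining its neighbours gives 932.5, which is too high; omitting day 2 gives 912.5. The peak changes only if day 1 is missed.
- **That a definite loss of power on AUC can be computed.** The design effect is for peak ALT, and nothing supports a model in which draws are missed independently.

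**Conclusion.** The point holds as a conflict between two sections and a stated exclusion after randomisation. Under the text as written, the main comparison of peak and AUC is in effect a completers' analysis, despite its modified intention-to-treat label.

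The consequence is a possible bias whose size the documents cannot settle. On the assumptions shown, it runs from zero to about 18.5 IU/L in peak ALT, or 31% of the target difference. The upper end needs a full SD shift, either confined to one arm with 10% missing in each, or in both arms with 5% against 15% missing. The article does not establish that withdrawal differed between arms, and a reader should not infer that it did. The matter deserves correction because part of the data needed to reduce the risk is already to be recorded.

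**What to change.** 1. In the withdrawal section, delete "However, these data will not be analyzed" as far as ALT and AST are concerned, and reconcile that section with the Statistical analysis section.
2. Include in the main comparison every randomised and operated patient with any postoperative ALT or AST value. Impute the individual missing daily values, for example on the log scale, by arm, from the other days and the preoperative value. Derive peak and AUC in each completed dataset and pool the arm difference. State separately how deaths are handled; the plan now lists death with the other causes of missing data, and values after death should not simply be imputed.
3. Keep the completers' result as a sensitivity analysis. Add a delta-adjusted imputation that shifts the imputed values in one arm until the conclusion changes, and report that shift, because standard imputation does not explore departures from missing at random.

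The cost is wording and analysis time; no new data collection is proposed. There are two drawbacks. The main estimate will depend on an imputation model, which has to be written down. And the Trial status section says the data were unblinded on 16 July 2023, so the change must be reported as made after unblinding, with the analysis as now planned shown beside it. This matters the more because the article already dates its choice of primary outcomes and its multiplicity adjustment after that day.

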### Sample size

This trial is originally conceived by the statistical and clinical teams with a total of 270 patients (135 within each group). It is based on our previous RCT [10] and the other relative RCT in our center [27]. In our previous study, the standard deviation (*σ*) of the postoperative serum peak ALT value is 184.684, AST value is 141.1 between two groups, and the target difference (*δ*) is 58.882 IU/L. The sample size calculated using peak ALT value is larger than using peak AST value. Thus, we estimate a sample size of 135 patients in each group to achieve an 80% statistical power (Uβ = 0.84, 1-sided test) at the 5% significance level (Uα = 1.645, 1-sided test) as well as an estimated dropout rate of approximately 10%.

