Of course, we also knowledge that preoperative steroids administration may arise some negative effects, such as inhibition of liver regeneration, gastrointestinal bleeding, and infection. However, Glanemann et al. have demonstrated that preoperative steroids administration has no apparent effects on hepatic regeneration [32]. Furthermore, liver regeneration has a close relationship with IL-6 that the overproduction of IL-6 inhibits liver regeneration [33]. As for gastrointestinal bleeding, dexamethasone administration should be cautious in patients after hepatectomy [34]. We will routinely use proton pump inhibitors. Administration of glucocorticoids may cause postoperative infections due to elevation of blood glucose. However, a recent RCT demonstrates that administration of preoperative single-dose methylprednisolone in patients undergoing a subsequent major liver resection lowers the risk of postoperative complications and surgical site infections as well as results in a shorter length of hospital stay [35]. Therefore, the trial protocol is reasonable and the results of the trial may be clinically significant.

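### The four primary tests alone are one-sided (family-wise 5%, 1.25% each) with no reason given, and the stated 80% power does not hold at the level actually used

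*Protocol article*

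**What the plan says.** The Sample size section sets the error rates: "to achieve an 80% statistical power (Uβ = 0.84, 1-sided test") and "at the 5% significance level (Uα = 1.645, 1-sided test"). It takes the SD from the group's earlier trial ("postoperative serum peak ALT value is 184.684, AST value is 141.1 between two groups") and a target difference that "is 58.882 IU/L. The sample size calculated using peak ALT value is larger than using peak AST value". It adds "an estimated dropout rate of approximately 10"% and concludes: "Thus, we estimate a sample size of 135 patients in each group to achieve an 80% statistical power".

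The Statistical analysis section then separates the primary tests from the rest: "All tests for differences except primary outcomes are two-tailed and considered statistically significant if" P is below 0.05. It applies a Bonferroni correction over the four primary outcomes, makes primary superiority a condition for testing the secondary outcomes, and repeats the 80% power figure. It does not name the alpha to which the correction applies, since its 0.05 sentence leaves the primary outcomes out. The only level given for them is the one-sided 5% in the Sample size section. Neither section gives a reason for testing in one direction only.

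**The concern.** The outcomes that decide the trial are the only ones tested in one direction. A one-sided family at 5% allows twice the chance of a false claim of benefit that a two-sided 5% family allows. Because primary superiority opens the way to the secondary tests, that choice also governs whether any later claim can be made. In the other direction, higher ALT or AST on dexamethasone could not be called significant, however large the difference.

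The power statement is affected too. It was worked out for a single one-sided test at 5%, whereas the stated analysis divides alpha by four. A reader who relies on the 80% would misjudge what a non-significant result means.

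**Working it through.** **Inputs (Sample size section).** SD of peak ALT 184.684; difference 58.882 IU/L; z for alpha 1.645; z for power 0.84; dropout about 10%; 135 per group. Bonferroni over four outcomes comes from the Statistical analysis section.

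**1. Reproduce the stated size.**
n = 2 × [SD × (z_alpha + z_beta) / difference]²
= 2 × [184.684 × (1.645 + 0.84) / 58.882]² = 121.5 evaluable per group.
121.5 / 0.9 = 135.0 per group, as stated. A two-sided 5% test with the same inputs needs 155 evaluable, or 173 with dropout. The 135 therefore rests on an unadjusted one-sided 5% test.

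**2. False-positive bound in the direction of benefit.**
- One-sided family at 5%: 0.05 / 4 = 0.0125 per test; bound 4 × 0.0125 = 5%.
- Two-sided family at 5%: 0.0125 / 2 = 0.00625 per test in that direction; bound 4 × 0.00625 = 2.5%.
- If the four tests were independent: 1 − 0.9875⁴ = 4.91% and 1 − 0.99375⁴ = 2.48%.

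Bonferroni lowers the level of each test but leaves the factor of two for the family.

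**3. Power for peak ALT at the planned size.** Normal approximation: power = Φ(D − z_crit), where D = (58.882 / 184.684) × √(121.5 / 2) = 2.485.

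| Test level | z_crit | Power, 121.5 per group | Power, all 135 evaluable |
|---|---|---|---|
| One-sided 0.05 (used for sizing) | 1.645 | 80.0% | 83.5% |
| One-sided 0.0125 (stated analysis) | 2.24 | 59.6% | 64.7% |
| Two-sided 0.0125 | 2.50 | 49.5% | 54.8% |

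Most of the loss (80.0% to 59.6%) comes from Bonferroni. Sidedness accounts for the further step to 49.5%.

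**4. Other primary outcomes.** If the same 58.882 IU/L applies to peak AST (SD 141.1), power with 121.5 per group is 84.4% at one-sided 0.0125 and 77.5% at two-sided 0.0125. No SD is given for either AUC, so their power cannot be checked.

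**5. Intervals.** A two-sided test at 0.0125 matches a 98.75% interval, with half-width 2.50 standard errors. An estimate between 2.24 and 2.50 standard errors in favour of dexamethasone would be positive one-sided while its 98.75% interval still included no difference.

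**The case against.** The strongest reply is that a one-sided superiority test is a legitimate design, is stated openly, and is used consistently in the sizing and the analysis. The Background cites earlier trials with favourable AST and ALT changes, so the expected direction has some support. That stands as far as it goes: there is no contradiction over sidedness and no arithmetic error in the 135. But expecting benefit does not rule out the opposite effect, and the article does not argue that it does.

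It is also fair that re-sizing is pointless. The Trial status section records recruitment complete on 1 April 2023 and unblinding on 16 July 2023.

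Four stronger readings are tempting, and the article does not support them:

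- *Each primary test is looser than a secondary test.* It is not. One-sided 0.0125 needs z = 2.24, while a two-sided 5% secondary test needs 1.96. The factor of two appears only when the primary family is compared with a two-sided 5% family.
- *A 95% interval could include no difference while the primary test is positive.* Not for a t test under the stated plan, since 2.24 exceeds 1.96. The mismatch arises only with the adjusted 98.75% interval.
- *Two-sided primary tests would show the harms that the protocol raises.* The Discussion says "preoperative steroids administration may arise some negative effects, such as inhibition of liver regeneration", and also names gastrointestinal bleeding and infection. ALT and AST do not measure these. Postoperative complications are a secondary outcome and fall under the two-tailed rule. What restricts their formal testing is the requirement of primary superiority first, which is a different matter.
- *The one-sided test was chosen after unblinding.* The article dates the choice of primary outcomes and the change in multiplicity adjustment to after 16 July 2023. It does not date the sidedness. The 270 is described as the original figure and reproduces only with a one-sided 5% test, which points to an early choice.

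**Conclusion.** The point holds in this form. The primary family is one-sided at a family-wise 5%, unlike every other test and without a stated reason. The bound on a false claim of benefit is 5% rather than 2.5%, and worse transaminases on dexamethasone could not be declared significant. The 80% power does not describe the stated analysis: for peak ALT it is about 60% one-sided and about 49% two-sided after Bonferroni.

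This rests on three assumptions: the Bonferroni correction divides the one-sided 5% of the Sample size section; the article's SD and difference are right; and dropout is 10%. With no dropout the figures are 64.7% and 54.8%. They are per-test powers for peak ALT. The chance that at least one of the four tests succeeds depends on correlations and AUC SDs that the article does not give.

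The point limits the strength of a claim of benefit and should be corrected, but it does not invalidate the trial. Whether the multiplicity rule should have changed after unblinding is a separate question.

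**What to change.** Test the four primary outcomes two-sided at a family-wise 5% (0.0125 each) and report 98.75% confidence intervals. If the one-sided test was demonstrably fixed before unblinding, keep it, report the two-sided adjusted P values and 98.75% intervals beside it, and state the one-sided level openly in the conclusion.

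In both the Sample size and Statistical analysis sections, restate the power for peak ALT at the level actually used (about 60% at one-sided 0.0125, about 49% at two-sided 0.0125), and say that the 135 per group was derived from an unadjusted one-sided 5% test. Do not re-size.

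The cost is wording and reporting only, with no extra patients. The stated power becomes less favourable, and under the two-sided rule an estimate between 2.24 and 2.50 standard errors in favour of dexamethasone would no longer count as positive. Made after unblinding, the change to two-sided testing can only make a claim of benefit more conservative.
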